## Abstract

**Background:** Diabetes is common among nursing home residents, with approximately one in four affected, a figure expected to rise. Despite the complexity of care required, educational support for nursing home staff remains limited. This study will aim to co-design and evaluate a digital intervention to improve staff knowledge, confidence, and practices in diabetes care. **Methods:** The study will follow a logic model across three workstreams. Workstream 1 (WS1) will inform the model inputs through three phases: (1) a scoping review will be conducted to summarise existing diabetes education initiatives in nursing home settings; (2) approximately 20 semi-structured interviews will be carried out with nursing home staff to explore perceived barriers and supports in delivering diabetes care; and (3) a modified Delphi process involving 50–70 diverse stakeholders will be used to establish educational priorities. Workstream 2 (WS2) will involve co-designing a digital diabetes education intervention, informed by WS1 findings. Co-design participants will include nursing home staff, diabetes professionals, and people living with diabetes or their carers. Workstream 3 (WS3) will consist of a mixed-methods evaluation of the intervention. Pre- and post-intervention questionnaires will assess staff knowledge, confidence, and attitudes. The usability of the intervention will also be measured. Following implementation, focus groups with approximately 32 staff members will be conducted to explore user experiences and perceived impact on resident care. **Discussion:** This study will address an important gap in staff education and support, aiming to improve diabetes care within nursing home settings through a digitally delivered, co-designed intervention.

## 1. Introduction

Diabetes is a chronic and increasingly prevalent global health issue, affecting approximately 537 million people (10.5% of the global population), with projections rising to 643 million by 2030 and 783 million by 2045, predominantly in low- and middle-income countries (LMICs) where healthcare systems often struggle to manage the burden [1,2]. It is characterised by elevated blood glucose levels due to insufficient insulin production or ineffective insulin use [3,4], and includes Type 1, Type 2, gestational, and rarer forms like monogenic diabetes and latent autoimmune diabetes in adults (LADA) [5]. Type 1 diabetes is autoimmune, while Type 2, accounting for 90–95% of cases, is linked to obesity, inactivity, and unhealthy diets [6,7], and though manageable with lifestyle changes and medication, often leads to serious complications such as cardiovascular disease and kidney problems [3]. The condition imposes a massive economic burden, with diabetes-related healthcare costs reaching USD 966 billion and expected to exceed USD 1 trillion by 2045 [2]; globally, the economic impact exceeds USD 760 billion [8], and individuals with diabetes incur healthcare costs 2.3 times higher than those without the condition [9]. Without effective intervention, the global diabetes burden will continue to grow, demanding coordinated international action to improve healthcare access, encourage healthier lifestyles, and implement preventive strategies [4].

The rise in life expectancy and the growing number of older adults has contributed to the increasing prevalence of diabetes in nursing homes, where up to 25–34% of residents have the condition [10]. Older adults with diabetes are often managing multiple comorbidities, such as cardiovascular disease, neuropathy, nephropathy, and cognitive decline, making diabetes management more complex [11]. In addition, many nursing home residents have diminished functional capacity, frailty, and varying degrees of cognitive impairment, which exacerbate the challenges of diabetes care [12]. This complexity highlights the need for individualised care plans that address not only the medical aspects of diabetes but also the unique needs of each resident, including mobility, nutrition, and cognitive health [13], while recognising the essential role of non-pharmacological interventions in complementing effective medications to support holistic care.

Diabetes management in nursing homes involves regular blood glucose monitoring, appropriate medication administration, and tailored nutritional interventions. These strategies are essential not only for preventing acute complications, such as hypoglycaemia and hyperglycaemia, but also for mitigating long-term risks, such as cardiovascular disease and neuropathy [4,14]. Nursing home staff play a critical role in managing diabetes for their residents, yet research has shown that many staff members lack the necessary education and training to effectively manage the condition [15]. This knowledge gap can lead to suboptimal care and poorer outcomes for residents living with diabetes [16]. Furthermore, the increasing prevalence of diabetes in nursing homes has highlighted the importance of preventive interventions aimed at reducing the onset of diabetes. Lifestyle modifications, such as diet and exercise, have been shown to play a crucial role in maintaining healthy glucose levels and preventing the progression from prediabetes to Type 2 diabetes [17]. For nursing home residents, facilitating regular physical activity and providing nutritious meals tailored to individual dietary needs can significantly improve health outcomes and overall well-being [16].

Despite the known challenges and complexities of diabetes management in nursing homes, there remains a critical need for enhanced diabetes education and training for nursing home staff. Comprehensive education on diabetes can equip staff with the necessary knowledge to administer medications correctly, monitor glucose levels effectively, and respond to changes in residents’ health status [18,19]. Additionally, empowering residents to take part in their own diabetes management, where feasible, can promote independence and improve quality of life [20]. Given the growing number of nursing home residents living with diabetes and the associated healthcare challenges, there is an urgent need to develop and implement interventions that support effective diabetes management in these settings [17,21]. In the United Kingdom, nursing homes provide long-term care for older adults with complex health needs, including those with diabetes [22]. Admission to a nursing home typically follows a comprehensive assessment of an individual’s medical, functional, and social needs, often initiated by healthcare professionals or social services in consultation with families [23]. Nursing homes are staffed by a multidisciplinary team, including registered nurses, care assistants, managers, and, in some settings, allied health professionals such as occupational therapists and physiotherapists [23]. Staff educational backgrounds vary, with registered nurses holding professional qualifications and care assistants typically having vocational training [24].

A key area of focus is the co-design and testing of digital interventions, which can provide real-time support and education for both nursing home staff and residents. Digital tools hold significant potential to improve diabetes management by facilitating continuous monitoring, delivering tailored educational content, and supporting individualised care plans [25]. By addressing the unique challenges of managing diabetes in nursing homes, these interventions may help optimise the quality of life for residents and improve overall care outcomes. Given the non-clinical nature of this intervention, its effects will be evaluated using validated self-report instruments measuring changes in self-efficacy, knowledge, and communication practices. This approach allows for understanding of behavioural and attitudinal shifts that may result from the educational content. There is a notable paucity of educational interventions specifically designed to support care home staff in managing diabetes, with digital approaches being even more scarce. This study addresses this gap by developing and evaluating a novel, co-designed digital intervention tailored to the unique needs of nursing home settings.

Therefore, the aim of this study is to co-design and evaluate a digital intervention to improve nursing home staff knowledge, self-efficacy (confidence, as measured by a validated self-efficacy questionnaire), and practice related to the care of residents living with diabetes.

## 2. Methods

### 2.1. Design

Logic modelling will guide the design of this interventional study, facilitating improved research planning by identifying theoretical and practical gaps and informing decisions regarding data collection and analysis methods [26]. This study will follow best practices as outlined in the NIHR framework for complex interventions [27], unfolding across three primary workstreams: theorisation, where we will integrate established theories to inform our intervention’s design; co-design of the digital intervention, which will involve engaging patients and experts to collaboratively develop the intervention based on insights from the theorisation phase; and mixed-methods evaluation, focusing on proximal outcome testing to assess the intervention’s effectiveness. By embedding theory into each stage of the process, we aim to ensure that our intervention is not only tailored to meet identified needs but also rigorously evaluated [25], ultimately contributing to a robust evidence base for effective health interventions. As this study is not a clinical trial, it has not been formally registered.

**Workstream 1: Theorisation**

Workstream 1 (WS1) will contribute to the ‘inputs’ of the logic model and will be executed in three phases. The first two phases will occur concurrently, followed by the third phase upon their completion. WS1 is expected to be completed within the first 12 months of the study. Its aim is to gather evidence at global (scoping review), national (Delphi study), and local (qualitative interviews) levels to inform the development of the digital educational intervention.

**WS1 phase 1: Scoping review**

Phase 1 will involve conducting a scoping review of the literature to synthesise existing evidence on interventions within nursing homes aimed at enhancing care for residents with diabetes. A review protocol can be found here: https://osf.io/ge7nq/ (accessed on 24 April 2025). This phase will address the following objectives:What interventions have been implemented, if any, to improve diabetes care for residents in nursing homes?Have these interventions proven effective in improving diabetes care in nursing homes?What are the reported experiences of nursing home staff in delivering interventions for improving diabetes care, including the challenges, facilitators, and barriers they have encountered?

The findings from this review will inform both WS2 and WS3. The review will be conducted in accordance with Joanna Briggs Institute [28] recommendations and the PRISMA-ScR reporting standards for scoping reviews [29]. Searches will be conducted in the following databases: CINAHL Plus, Medline, PubMed and PsycINFO. Example search terms will include ‘diabetes’, ‘diabetic’, ‘nursing homes’, ‘residential homes’, ‘education’, and ‘training.’ Reference lists of relevant systematic and scoping reviews will be manually searched to identify additional studies not located in the initial search. The review will include studies that evaluate diabetes education interventions for nursing home staff, regardless of delivery mode, provided they report outcomes such as improvements in staff knowledge or resident quality of life. Studies focusing solely on outcomes related to diabetes management (e.g., drug prescribing and symptom monitoring) will be excluded, as will non-interventional studies, studies lacking a clear association with diabetes, and studies not conducted exclusively in nursing home settings.

**WS1 phase 2: Qualitative Interviews with Nursing home Staff**

Individual, semi-structured qualitative interviews will be arranged with staff members working in both nursing and residential care homes. The primary aim of these interviews is to explore the factors that support or hinder the delivery of care to residents living with diabetes. All interviews will be conducted remotely using Microsoft Teams to facilitate participation and accessibility. Qualitative data gathered will provide an understanding of current challenges and enablers, directly informing the collaborative design process for the digital intervention in Workstream 2 (WS2).

Consistent with best practice guidance for qualitative research, we plan to recruit around 20 participants. Recruitment will continue until thematic saturation is achieved, ensuring a comprehensive capture of relevant perspectives. Staff will be invited to participate via convenience sampling from the Northern Ireland Nursing Home Research Network at Queen’s University Belfast (QUB), which comprises over 400 registered nurses active in the sector. This network’s members have previously agreed to be contacted for research, quality improvement, or educational activities. Potential participants will be approached through email invitations. Nursing home staff are defined as all employees providing direct care to residents, including registered nurses and care assistants who are involved in direct resident care.

The participants’ levels of experience are expected to vary, with eligible participants including home managers, charge nurses, registered nurses, care assistants who provide direct care to residents with diabetes. To be eligible, participants must have been practising within the nursing home setting for more than six months and provide nursing care to residents living with diabetes.

**WS1 phase 3: Delphi study**

A modified Delphi study will be conducted to identify the key educational priorities related to diabetes, as perceived by relevant stakeholders. This study will build on findings from the preceding scoping review and individual interviews. The initial Delphi items will be developed by the research team based on empirical data obtained during phases 1 and 2 of Workstream 1 (WS1). The Delphi method is a structured process for eliciting expert opinion through multiple rounds of questionnaires, allowing for anonymous responses and iterative reflection. This approach facilitates the development of consensus on complex issues through controlled feedback [30].

The study will consist of three rounds of online surveys administered to stakeholders across the United Kingdom (England, Scotland, Wales, and Northern Ireland). Stakeholder groups will include nursing home staff, diabetes practitioners, individuals living with diabetes, carers, educationalists, community dietitians working in care home settings, and representatives from relevant charitable organisations. Recruitment will be supported by the Royal College of Nursing’s Older People Forum, a UK-wide professional network comprising approximately 12,000 members involved in the care of older adults. Additional participants will be recruited via the research team’s professional networks.

Based on prior Delphi studies, it is expected that a sample of 50 to 70 stakeholders will be recruited [25]. Surveys will be administered using Microsoft Forms and distributed to participants who have provided informed consent. Following the completion of the third survey round, an online consensus meeting will be held. During this meeting, stakeholders will anonymously vote on the educational priorities to be used in the co-design of the digital intervention developed in Workstream 2 (WS2). The Delphi process is expected to be completed over a six-month period, allowing time for survey distribution, response collection, and data analysis.

**Workstream 2: Co-design of the digital intervention**

Guided by the findings from Workstream 1 (WS1), Workstream 2 (WS2) will centre on the co-design and development of a digital intervention. The co-design methodology entails iterative and collaborative engagement between the research team, software developers, and end-users [31,32,33,34,35], ensuring alignment between technological functionality and user requirements. This collaborative approach is intended to enhance the usability, acceptability, and overall effectiveness of the intervention [36]. The digital intervention will constitute the primary ‘output’ within the corresponding logic model framework.

The co-design process will involve approximately 20 participants, comprising a balanced representation of key stakeholder groups: five individuals with lived experience of diabetes or their carers, five healthcare professionals with diabetes expertise, five staff members from nursing homes, and five members of the research team with clinical or academic expertise in diabetes care and residential aged care settings. Participant recruitment will be managed by the research team to ensure broad stakeholder representation. An external technology partner will be actively engaged throughout the co-design process, attending all sessions and offering real-time input on prototype development and refinement.

The co-design group will convene once per month over a four-month period. The initial session will introduce participants, facilitate knowledge-sharing based on lived and professional experiences, and present key insights from WS1. The second session will prioritise identifying core objectives and functional requirements of the intervention. The third session will focus on refining content, including ensuring that language is accessible and appropriate for the intended end-user audience. The final session will concentrate on visual and usability aspects, such as layout, navigation structure, and colour palette. These iterative workshops are designed to ensure the intervention is user-centred and contextually appropriate. All meetings are expected to occur in person, in alignment with international best practice guidelines for co-design processes [31,32,33,37,38,39,40,41].

**Workstream 3: Intervention testing**

Workstream 3 (WS3) will involve intervention testing of the digital intervention, using a mixed-methods approach to assess its outcomes, which will form the final phase of the study. The digital intervention will be implemented over a period of 12 weeks, during which nursing home staff will have access to the educational materials and complete pre- and post-intervention assessments.

**WS3 phase 1: Nursing home staff knowledge, self-efficacy, and usability**

In phase 1, nursing home staff knowledge and self-efficacy in providing care for residents with diabetes will be assessed before and after implementing the digital intervention via a pre- and post-test questionnaire. The questionnaire, delivered electronically through the intervention, will include the Michigan Diabetes Knowledge Test (DKT2) (twenty-three items) [42] and an eight-item questionnaire on self-efficacy in providing care to residents with diabetes. The Michigan Diabetes Knowledge Test (DKT2) is a widely validated tool used to assess general diabetes knowledge and has demonstrated good internal consistency (Cronbach’s alpha = 0.77) [42]. The self-efficacy questionnaire was adapted from established scales used in similar care settings, with items reviewed by experts during the co-design process to ensure face validity. Approximately 100 registered nurses will be recruited from ten nursing homes across Northern Ireland. These homes will represent both rural and urban settings. A power calculation will not be required as we plan to conduct proximal testing as per NIHR guidelines on complex interventions [27]. However, the anticipated sample of approximately 100 registered nurses from 10 nursing homes is consistent with recommendations for feasibility and proximal outcome testing in complex intervention research [27]. This sample size allows for preliminary evaluation of changes in knowledge and self-efficacy, while also accounting for expected attrition in this population. Analytics, such as user engagement and time spent on the platform, will also be analysed to evaluate the intervention’s usability. Usability will be further evaluated using the 31-item User Engagement Scale (UES) questionnaire [43], which will address the ‘practicality’ aspect of the testing. The User Engagement Scale (UES) has robust psychometric properties, including strong reliability and construct validity in digital health education contexts [43]. The selection of these tools was guided by their proven validity, relevance to the target population, and alignment with the intervention’s educational objectives.

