**WS3 phase 2: Staff experience on implementation**

Phase 2 will focus on understanding nursing home staff experiences of implementing the intervention and their perceived impact of the educational intervention on their practice and resident care. Focus groups (*n* = 4) will be conducted with up to 32 nursing home staff, including managers and nurses. Depending on data saturation, participant numbers may be adjusted. Recruitment will follow the completion of the post-test questionnaires in phase 1, with participants offered the opportunity to join the focus groups.

Table 1 provides an overview of workstreams and phases for this study.

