#### 2.2.2. Quantitative Analysis

Quantitative data will be analysed using IBM SPSS Statistics, version 26. Descriptive statistics will be used to summarise findings from the modified Delphi study (WS1) as well as platform-generated internal analytics collected during the evaluation phase (WS3). These analytics include metrics such as the duration of time care staff engage with the digital intervention. To evaluate changes in nursing home staff knowledge and self-efficacy following exposure to the intervention, dependent (paired samples) *t*-tests will be conducted as part of WS3. This analysis will provide a preliminary indication of the intervention’s potential effectiveness.

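### Outcome tests are delivered inside the platform and analysed in pairs, so WS3 measures change in nurses who return to the platform; the pre-test timing is also stated in two ways

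*Protocol article*

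**What the plan says.** All statements are in the Protocol article.

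- **Route of measurement** (WS3 phase 1): "The questionnaire, delivered electronically through the intervention, will include the Michigan Diabetes Knowledge Test (DKT2") and an eight-item self-efficacy questionnaire. No other route is named.
- **Timing, first statement** (WS3 phase 1): knowledge and self-efficacy "will be assessed before and after implementing the digital intervention via a pre- and post-test questionnaire".
- **Timing, second statement** (Workstream 3: Intervention testing): implementation lasts 12 weeks, and this is described as the period "during which nursing home staff will have access to the educational materials and complete pre- and post-intervention assessments".
- **Sample** (WS3 phase 1): about 100 registered nurses from ten homes, a number justified in part as "while also accounting for expected attrition in this population". No attrition rate is given.
- **Analysis** (section 2.2.2): the method is that "dependent (paired samples) *t*-tests will be conducted as part of WS3". Its purpose is given as change in staff knowledge and self-efficacy after exposure. The same section calls the result preliminary.
- **Focus groups** (WS3 phase 2): "Recruitment will follow the completion of the post-test questionnaires in phase 1, with participants offered the opportunity to join the focus groups".

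**The concern.** When the post-test can be reached only through the platform, supplying an outcome requires the same behaviour as using the intervention. A nurse who stops logging on is both less exposed and less likely to be measured. The Discussion names plausible reasons for not returning: limited digital literacy, uneven access to devices and internet, resistance to change, and staff turnover. The first three also bear on how much a nurse would learn.

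The stated target is change in nursing home staff, but the quantity estimated is change in nurses who came back. The Discussion acknowledges the lack of randomisation and the short follow-up, but not this restriction. It also links positive results to further testing and scale-up, so a gain measured only in returners would be a poor planning figure for the larger randomised studies it calls for. Post-tests not collected during WS3 cannot be recovered at analysis.

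The two timing statements raise a second, smaller issue. One puts the pre-test before implementation; the other puts both tests in the period when the materials are open. If some nurses took the pre-test after seeing content, their baseline would already contain part of the gain.

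**Working it through.** The article gives no attrition rate, effect size or standard deviation, so there is no stated figure to reproduce. What follows is illustrative and in relative terms.

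**1. Loss of non-returners**

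Inputs: N = 100 nurses (WS3 phase 1); d = share without both tests, assumed 20%, 30% or 40%; r = gain of those nurses relative to completers, assumed 0, 0.5 or 1.

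Mean gain in all recruited ÷ gain in completers = (1 − d) + d × r. Overstatement = 1 ÷ [(1 − d) + d × r] − 1.

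| d | Pairs left | r = 0: ratio, overstatement | r = 0.5: ratio, overstatement | r = 1 |
|---|---|---|---|---|
| 20% | 80 | 0.80, 25% | 0.90, 11% | 1.00, 0% |
| 30% | 70 | 0.70, 43% | 0.85, 18% | 1.00, 0% |
| 40% | 60 | 0.60, 67% | 0.80, 25% | 1.00, 0% |

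The r = 1 column is the case where missingness is unrelated to gain.

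**2. Late pre-test**

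Inputs: f = share taking the pre-test after seeing content, assumed 10%, 25% or 50%; g = share of the gain already acquired by then, assumed one half.

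Observed gain ÷ true gain = 1 − f × g:

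- f = 10%: 1 − 0.10 × 0.5 = 0.95
- f = 25%: 1 − 0.25 × 0.5 = 0.875
- f = 50%: 1 − 0.50 × 0.5 = 0.75

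If nobody takes it late, the ratio is 1.

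**3. Both together**

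Applying step 2 to the completers, reported gain ÷ mean gain in all recruited = (1 − f × g) ÷ [(1 − d) + d × r].

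- d = 20%, r = 0, f = 25%: 0.875 ÷ 0.80 = 1.09, a net overstatement.
- d = 20%, r = 0.5, f = 25%: 0.875 ÷ 0.90 = 0.97, a net understatement.

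The sign therefore depends on quantities that the article does not give.

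**4. Would a mixed model cure step 1?**

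Suppose nurses without a post-test gain nothing but have the same baseline scores as the others. A model with time, fitted to everyone with a pre-test, fills in their post-test mean from the observed post-tests under a missing-at-random assumption. Baseline carries no information about who failed to gain, so the estimate stays at the completers' gain. The model helps only as far as the observed data predict the missing scores.

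**The case against.** The strongest points on the other side are these.

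- **Missing-data rules and analysis sets may be in a full protocol or SAP that is not shown.** This stands, and their absence is not criticised here. The route of measurement, however, is stated outright, and no later analysis rule can supply post-tests that nurses away from the platform never completed.
- **Loss may have nothing to do with engagement.** The Discussion cites high staff turnover, and a nurse who changes job may have learned as much as anyone. This stands as a possibility and is the 0% case above. The dependence on engagement follows from the delivery route as a risk; it is not an established fact.
- **The baseline may be sound.** A reader might infer that the pre-test is uncontrolled, or that nurses may take it after the content opens. The article does not say so. WS3 phase 1 states the opposite intent, and platform delivery could just as well enforce the pre-test at first log-in. What remains is two statements that need reconciling. Nor does the article suggest that the post-test may be taken soon after a piece of content; after a 12-week implementation, the natural reading is about week 12.
- **The focus groups may not be restricted.** The recruitment sentence in WS3 phase 2 reads most naturally as sequence, with phase 2 recruiting once phase 1 testing is over. It does not make an individual's post-test a condition of invitation, and managers are included. Only a clarification is warranted.
- **The aim is modest.** Section 2.2.2 calls the result preliminary, and the Discussion urges caution and mentions possible selection bias. This stands and lowers the severity.

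**Conclusion.** The point holds in a limited form. Platform-only delivery, expected attrition and a paired t-test together make the WS3 estimate a change among returning platform users, while the stated target is nursing home staff. At an assumed 20% to 40% missing, the overstatement runs from 0% (missingness unrelated to gain) through 11% to 25% (non-returners gain half as much) to 25% to 67% (they gain nothing). The last range is the extreme case, and every figure rests on assumed inputs.

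A reader might conclude that the design must flatter the intervention. The documents do not support that. Selective loss inflates the gain only if non-returners gain less, and any late pre-test works the other way, so the net direction is unknown. Because the analysis is described as preliminary, this is something that should be fixed before WS3 begins rather than a fault that undermines the study.

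**What to change.** 1. Send the post-test by a link outside the platform, with reminders, to every enrolled nurse in a fixed window at the end of week 12, whatever their platform use. This is the change that matters most.
2. Reconcile the two timing statements by requiring the pre-test before any content opens.
3. Report the numbers recruited and with each test, and compare baseline scores and platform use between nurses with and without a post-test. The platform analytics are already planned.
4. State in WS3 phase 2 that focus-group invitations go to all enrolled staff, including low users.
5. A mixed model using everyone with a pre-test may be added, but it does not replace item 1.

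The cost is one survey link, reminder e-mails, a platform setting and a few lines of reporting. No extra participants or control group are needed. The likely downside is a smaller reported gain.
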